Previous studies have investigated the feasibility and efficacy of lifestyle interventions in breast cancer patients and obese women, in terms of recruitment, compliance and weight loss [42,43,87,88]. Some studies have also examined the effects of lifestyle interventions on aspects of psychological [41,47,71,72] and physiological [42,87,88] well-being. However, no previous studies have investigated the effects of a dietary and exercise intervention on a range of important prognostic breast cancer biomarkers that could be strongly influenced by weight loss and improved psychological well-being. Thus, the aim of the intended research is to examine the effects of a dietary and exercise intervention on body weight, indices of psychological well-being and biomarkers associated with disease recurrence and physiological health status in female breast cancer survivors. We hypothesize that the lifestyle intervention will evoke a reduction in body weight and an improvement in psychological well-being. Secondly, that improvements in blood markers of cancer risk and physiological health status (estrogen, CRP, IL-6), psychosocial stress (cortisol and catecholamines) and immune function (lymphocyte proliferation and NK cell function) will be associated with changes in body weight and psychological well-being induced by the lifestyle intervention. Considered together, the results of this study would provide valuable new information to improve our understanding of the role that lifestyle-modifiable factors can play in saving or prolonging the lives of women who have been treated for breast cancer.

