### Secondary aims

1. To examine the relationship between change in body weight and biomarkers associated with disease recurrence and physiological health status, including circulating levels of estrogen, CRP and IL-6.

2. To examine the relationship between changes psychological health status, circulating stress hormones and indices of immune function.

3. To examine the effects of the dietary and exercise intervention on broader quality of life dimensions.

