### Details of power calculations and sample size

Body weight was chosen as the primary outcome variable for calculation of sample size. Utter *et al*. [88] reported a 8.1 kg reduction in body weight in obese women following a 12 week lifestyle intervention, incorporating moderate dietary energy restriction in conjunction with exercise. Body weight changed from a baseline ± SD level of 89.9 ± 11.7 to 81.8 ± 10.8 kg following the intervention. This amount of weight loss is associated with improved physical and psychological health in obese women [41,90]. On the basis of these data, and taking into account an expected patient drop-out of up to 10% (based on the drop-out rate in our ongoing trial with breast cancer survivors [91]), recruitment of 50 patients for each group will give us 90% power to detect a difference in body weight of 8 kg at the α level of 0.05.

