### Data Analysis

A mixed factorial ANOVA will be used to assess (i) changes from baseline on all outcome measures following the intervention within patient groups, and (ii) differences in outcome measures between patients in the lifestyle intervention and control groups post intervention. Pearson product moment correlation coefficients (r) will be calculated to determine bivariate relationships among changes in the variables. Statistical significance will be set at *p *< 0.05. All data will be analysed using the SPSS statistical package (SPSS UK Ltd, Woking, U.K.).

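### The correlations planned for secondary aims 1 and 2 take no account of randomised arm; if the arms are pooled, the group difference can create or inflate them

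*Protocol article*

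**What the plan says.** Two of the three secondary aims in the protocol article are about relationships between changes. Aim 1 is "To examine the relationship between change in body weight and biomarkers associated with disease recurrence and physiological health status", with estrogen, CRP and IL-6 named. Aim 2 is "To examine the relationship between changes psychological health status, circulating stress hormones and indices of immune function". The Background section states the matching hypothesis: improvements in the blood markers "will be associated with changes in body weight and psychological well-being induced by the lifestyle intervention".

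The Data Analysis section has one sentence on method for these aims: "Pearson product moment correlation coefficients (r) will be calculated to determine bivariate relationships among changes in the variables". The significance level is 0.05 throughout. The preceding sentence, on the mixed factorial ANOVA, refers explicitly to patient groups. The correlation sentence does not refer to groups, and it does not say whether the arms are pooled, analysed separately or adjusted for.

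Aim 3 is of a different kind: "To examine the effects of the dietary and exercise intervention on broader quality of life dimensions". It is a treatment-effect question, and the ANOVA covers it.

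**The concern.** The intervention is designed to lower weight and improve well-being, and the markers are expected to improve alongside. If it succeeds, arm is a common cause of both members of each correlated pair. Pooling then lines up two clusters of patients: one with little change in either variable, the other with change in both. That alone gives a correlation, even if the women who lost most weight within an arm had no larger marker change than the rest.

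A pooled r therefore mixes two things: the treatment effect on each variable, which the ANOVA already tests, and the patient-level relationship that aims 1 and 2 ask about. The larger the effects on both variables, the larger the unwanted part. At stake is a claim that marker change follows weight or mood change, when the data may show only that the intervention moved both, possibly by separate routes.

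**Working it through.** **The plan's own figure.** The sample-size section says that "recruitment of 50 patients for each group will give us 90% power to detect a difference in body weight of 8 kg at the α"; the value given for α is 0.05, with up to 10% drop-out allowed for. Its source data are: "Body weight changed from a baseline ± SD level of 89.9 ± 11.7 to 81.8 ± 10.8 kg following the intervention". With SD 11.7 kg, two-sided α 0.05 (sidedness is not stated) and 90% power, n = 2(1.960 + 1.282)² × 11.7² / 8² ≈ 45 per arm, and 45 / 0.9 = 50. The figure reproduces. It implies 45 completers per arm, 90 in all. The protocol gives no corresponding figure for the correlations.

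**Size of the weight effect on the change scale.** The SD of change is not given. With an assumed pre–post correlation ρ, SD of change = √(11.7² + 10.8² − 2ρ × 11.7 × 10.8), and d1 = 8 / SD of change:

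- ρ = 0.5: SD 11.3 kg, d1 = 0.71
- ρ = 0.8: SD 7.2 kg, d1 = 1.12
- ρ = 0.9: SD 5.1 kg, d1 = 1.57
- ρ = 0.95: SD 3.7 kg, d1 = 2.18

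**Correlation produced by pooling.** For two equal arms with within-arm correlation r_w and between-arm differences in change of d1 and d2 within-arm SDs:

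pooled r = (r_w + d1·d2/4) / √[(1 + d1²/4)(1 + d2²/4)]

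Example with r_w = 0, d1 = 1.12, d2 = 0.5: 0.14 / √(1.314 × 1.063) ≈ 0.12. The two-sided critical value at n = 90 is |r| = 0.207.

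**False-positive rate.** The table assumes r_w = 0, 45 per arm and 20,000 simulated trials per cell, with d1 rounded to 0.70, 1.12, 1.57 and 2.2. Marker effects d2 are assumed, because the protocol gives none. Entries are pooled r, then the share of trials with p < 0.05.

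| d2 | d1 = 0.70 | d1 = 1.12 | d1 = 1.57 | d1 = 2.2 |
|---|---|---|---|---|
| 0 | 0; 5% | 0; 5% | 0; 5% | 0; 5% |
| 0.2 | 0.03; 6% | 0.05; 7% | 0.06; 9% | 0.07; 10% |
| 0.3 | 0.05; 7% | 0.07; 11% | 0.09; 14% | 0.11; 18% |
| 0.5 | 0.08; 12% | 0.12; 20% | 0.15; 30% | 0.18; 41% |
| 0.8 | 0.12; 21% | 0.18; 41% | 0.23; 61% | 0.28; 77% |

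**Stress–immune pairs (aim 2).** No effect sizes are given. Rates are 5.1% at effects of 0.2/0.2 SD, 5.4% at 0.3/0.3, 8.8% at 0.5/0.5 and 13.5% at 0.8/0.5.

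**After adjusting for arm.** The partial correlation given group averages about 0, with a rejection rate of 4.7–5.2% in every scenario above.

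**When a real link exists.** With r_w = 0.3, d1 = 1.12 and d2 = 0.5, pooled r averages 0.37 and is significant in 96% of trials. The adjusted estimate averages 0.30 with about 82% power. Using the intervention arm alone (45 women) also gives about 0.30, but with 52% power.

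**The case against.** The strongest reply is that the protocol never says the arms are pooled. The hypothesis concerns changes brought about by the intervention, so correlations within the intervention arm are a possible reading, and they carry no between-arm artefact. That stands as far as it goes: pooling is an inference, drawn from a bivariate statistic that mentions no groups directly after an ANOVA sentence that does. It does not remove the point, because the text leaves the biased version open.

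It can also be said that the between-arm part of a pooled r is itself intervention-induced change, which the hypothesis is about. This stands in part. However, a pooled r does not isolate such a link: it is non-zero whenever both variables respond to treatment, even by unrelated routes.

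A reader might infer several stronger things that the documents do not support:

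- **That spurious links will appear.** They need an arm effect on both variables. If the marker does not move there is no artefact, and at modest effects it is small.
- **That any link found comes only from the group difference.** A true within-arm link also contributes, and is then inflated (0.30 to 0.37 in the example).
- **That the secondary aims cannot be answered.** Aim 3 is untouched, and aims 1 and 2 can be answered from the same data.
- **That the study's declared added value is lost.** The abstract ties that to the intervention's effects on biomarkers, which the ANOVA addresses.
- **That markers will be correlated untransformed, or that every pair of variables will be tested.** The protocol gives no marker distributions and does not rule out transformation; the secondary aims limit the relationships of interest. Both details are commonly left to an analysis plan.

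**Conclusion.** The point holds in a limited form. The only stated method for secondary aims 1 and 2 ignores arm and, if the arms are pooled, can create or inflate correlations. For weight–marker pairs at the design's 8 kg difference, the false-positive rate is about 7–18%, 12–41% and 21–77% for marker effects of 0.3, 0.5 and 0.8 SD, with the upper ends at a weight effect near 2.2 SD. For stress–immune pairs the problem is minor unless effects are large: about 9% at 0.5/0.5 SD.

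These figures rest on 45 completers per arm, a two-sided test, normally distributed changes with equal variance in the two arms, and assumed values for the pre–post weight correlation and the marker effects. The direction of the bias follows from the formula and does not depend on those values; its size does. The change should be made, but nothing here threatens the primary comparison.

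**What to change.** Replace the correlation sentence in Data Analysis with wording such as: for the pairs named in secondary aims 1 and 2, the association between changes will be estimated with adjustment for randomised group, as a partial correlation of the changes given group or as a regression of marker change on weight change (or psychological-score change) with group as covariate. For a given pair these two give the same test. Any pooled correlation will be reported as descriptive only, and pairs not named in the aims as exploratory.

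If correlation within the intervention arm was intended, the text should say so and accept the lower power of about half the sample.

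The cost is a change of analysis wording, with the same data and software. There are two drawbacks. Associations will generally look weaker than the pooled r. The adjusted estimate also leaves out the between-arm part of intervention-induced change, although the ANOVA already tests that part.
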